##### Language abilities

2.5.1.1

Language abilities will be assessed using two validated parental report instruments: The Infant–Toddler Checklist of the Communication and Symbolic Behavior Scales Developmental Profile [CSBS ITC (Wetherby and Prizant, 2002); Finnish version (Laakso et al., 2011)] and the standardized Finnish long form version of the MacArthur Communicative Development Inventories [Words and Gestures form, MCDI (Fenson et al., 1993); Finnish version (Lyytinen, 1999), Finnish Long Form version of the Communicative Development Inventories, FinCDI-LF]. Both methods have been normed for Finnish children and have shown to provide reliable information on the language skills of children [CSBS ITC (Laakso et al., 2011); FinCDI-LF (Lyytinen, 1999; Stolt et al., 2009)]. The CSBS ITC is a brief screening tool with three subscales (social, speech, and symbolic subscales) and a total score. The Words and Gestures form of the FinCDI-LF provides comprehensive information on children’s early receptive and expressive lexicons as well as on the development of early gestures. It gives scores separately for expressive and receptive vocabulary size and for the gestures scale for non-verbal communication.

##### Speech processing

2.5.1.2

In a multi-feature oddball paradigm with three deviant types embedded in a speech sound stream [speech sound paradigm described, e.g., in Virtala et al. (2022)], auditory ERPs are recorded with EEG in a passive listening condition at baseline and post-intervention assessments. Auditory ERPs in response to repeating standard stimuli (obligatory responses P1, N2) and occasional deviant stimuli (MMRs) are extracted from the EEG. Peak latencies, mean amplitudes, and hemispheric lateralization of these responses are quantified from a fronto-central region of interest.

#### Secondary outcomes

2.5.2

##### Language abilities

2.5.2.1

The standardized parental questionnaires (validated parental report instruments) CSBS ITC and MCDI/FinCDI-LF 16–30 mo will be re-administered to evaluate the language abilities at the follow-up assessment (Wetherby and Prizant, 2002; Laakso et al., 2011; Fenson et al., 1993; Lyytinen, 1999). The MCDI/FinCDI-LF 16–30 mo provides the size of expressive vocabulary and the mean length of the three longest utterances (in morphemes). The standardized language assessment test battery *Reynell Developmental Language Scales III (RDLS-III)* (Edwards et al., 1997; Reynell and Huntley, 2001); presented to the participants in Finnish (Kortesmaa et al., 2001) is conducted at post-intervention and follow-up assessment points and provides scores for expressive and receptive language abilities. It is relevant to acknowledge that at the post-intervention assessment point, the participants are still below the age range of the RDLS-III (younger than 2 years), and therefore, the scores obtained in this assessment will be treated with caution.

##### Speech processing

2.5.2.2

The speech sound paradigm described in 2.5.1.2 is re-administered with an identical protocol at the follow-up assessment.

#### Exploratory/other

2.5.3

##### Social–emotional factors

2.5.3.1

Three standardized parental questionnaires will be administered at all three assessment points to evaluate infant and early childhood temperament [Finnish translations of the Infant Behavior Questionnaire Revised short form, IBQ-R-sf (Putnam et al., 2014); Early Childhood Behavior Questionnaire short form, ECBQ-sf (Putnam et al., 2006, 2010)], social–emotional/behavioral problems, and delays in social–emotional competence [Finnish translation of the Brief Infant–Toddler Social Emotional Assessment, BITSEA (Briggs-Gowan et al., 2004)], as well as parental wellbeing, stress, and interaction with the child [Finnish translation of the Parenting Stress Index Short Form, PSI-sf (Abidin, 1995)]. The IBQ-R-sf and ECBQ-sf give scores for Negative Affectivity, Surgency/Extraversion, and Orienting/Regulation/Effortful Control. The PSI-sf consists of three factors: parental distress, parent–child dysfunctional interaction, and difficult child, as well as a total score. BITSEA consists of Problem and Competence scores.

##### Dyslexia risk and genetics

2.5.3.2

Parental dyslexia status is confirmed as part of the eligibility screening (see 2.1.2), coded in the database, and used as a stratification variable. DNA sampling is conducted from saliva (infants, parents) or blood samples (parents) at the post-intervention assessment (or at another assessment phase, according to the preferences of the family). Allele groupings in single-nucleotide polymorphisms (SNPs) of susceptibility genes associated with language, reading, and developmental dyslexia are analyzed from the sequenced DNA and used to form subgroups.

##### Musical abilities

2.5.3.3

At follow-up assessment, musical abilities will be investigated with a custom-made musicality test battery (the Music, Mind, Body, and Brain Music Battery, MMBB-MB; details of the battery will be reported in a separate publication), including melody (scale) and rhythm discrimination abilities, sensory–motor synchronization skills (including both whole-body movement and finger tapping), singing abilities, and perceived emotions in music.

##### Music processing

2.5.3.4

In a melodic multi-feature paradigm with several musical deviants embedded in a short melody [paradigm described, e.g., in Tervaniemi et al. (2022)], auditory ERPs are recorded with EEG in a passive listening condition at all three assessment points. The ERPs in response to repeating standard stimuli (obligatory responses P1, N2) and occasional deviant events (MMRs) are extracted from the EEG. Peak latencies, mean amplitudes, and hemispheric lateralization of these responses are quantified from a fronto-central region of interest.

##### Motor abilities

2.5.3.5

Fine and gross motor development will be evaluated with a custom-made parental questionnaire at all three assessment points and with a standardized test [Motor scale of the Bayley Scales III (Bayley, 2006), in Finnish] that includes sub-scales for fine and gross motor abilities at post-intervention and follow-up assessment points.

#### Background variables and parent-reported activities

2.5.4

At baseline, a custom-made parental questionnaire is administered to collect basic information on the following background variables: child’s age, gender, family structure, living situation and daycare situation, language background and exposure, genetic risk factors for neurodevelopmental, neurological, and psychiatric conditions, socioeconomic status (indicated by parental education and current employment status), physical growth (weight and height at birth and their development), as well as healthcare and illnesses of the child. At post-intervention and follow-up assessment points, possible changes regarding family structure, living and daycare situation, language background and exposure, genetic risk factors, as well as physical growth (height and weight) and healthcare and illnesses of the child will be inquired.

At all three assessment points, custom-made parental questionnaires are additionally used to collect information on the frequency and intensity of the child’s musical activities (including joint singing, dancing, moving to music, and playing instruments at home, music listening, and exposure to music at home), musical background of the parents (including preferences, training, and listening habits), home literacy environment (including the amount of reading by parents, the amount of reading aloud to the child, the amount of children’s and adults’ books at home, frequency of library visits, and audio book listening), screen time, and all regular hobbies that the child attends.

### Trial timeline

2.6

Recruitment started in March 2024, and the first family was enrolled in the study after randomization on 13 June 2024. Recruitment ended on 30 September 2025. The interventions are conducted between September 2024 and March 2026 (estimate). Altogether, 10 music interventions and 10 circus interventions will be conducted so that one music intervention and one circus intervention start nearly every month between September 2024 and October 2025 (estimate). The planned duration of all interventions is 5–7 months; however, all interventions consist of 20 weekly sessions with a fixed time (the number of canceled sessions and break weeks varies between interventions for practical reasons). Outcome measures will be collected at baseline (between August 2024 and September 2025), 6 months (post-intervention; between March 2025 and March 2026, estimate), and 1.5 years (follow-up, one year after post-intervention; between March 2026 and April 2027, estimate). Thus, data collection for primary outcome measures is estimated to be completed by March 2026 and for all outcome measures in April 2027.

By the end of recruitment and baseline assessments on 30 September 2025, 184 participants had been randomized to the study after providing oral consent. Of these, 154 participants had attended the baseline assessments and provided written informed consent (separate n’s according to strata: dyslexia-risk boys/dyslexia-risk girls/no risk boys/no risk girls *N* = 32/42/41/39; according to intervention arm: music/circus *N* = 75/79) with an average age of 10.17 months (SD 1.43, range 6.73–13.13; according to intervention arm: music/circus 10.18/10.14 months) at the first intervention session. Participants who were unable to attend the intervention sessions after providing written consent were nevertheless invited to all assessment points (see 2.9) unless they refused participation altogether. By the end of recruitment, one participating family with written consent had refused participation after the baseline assessment.

### Data management

2.7

The data involve digital and paper format data and biological samples. All digital data are stored on a University of Helsinki network drive in a group folder accessible only to the research group members and backed up by the university’s IT center. Digital data are stored in password-protected relational databases where they are transferred directly from the REDCap (questionnaires) or entered manually by the outcome assessors (behavioral test scores, EEG measurement protocols). All paper form data and biological samples are stored in locked premises and locked cabinets that can only be accessed by essential personnel of the research team. A collaborating laboratory (Folkhälsan Research Centre) will store the biological samples (saliva samples) and send them in pseudonymized form (without direct identifiers) to another laboratory for genetic laboratory analysis (DNA sequencing and targeted genotyping; procured as a contracted service); remaining samples will be returned to the collaborating laboratory for long-term storage (see below).

Data pseudonymization is performed during data collection, and all data analysis is conducted without direct identifiers. Direct identifiers are replaced by codes and stored separately in password-protected files. The passwords are only available to research team members who essentially need the information (e.g., contact information of the parents is only accessible to outcome assessors and the trial coordinator). Only the trial coordinator and, as a safety procedure, author PV, have direct access to the separate password-protected files that contain information on the arm allocation of the participants. This information will be included in the password-protected relational databases together with the rest of the digital data but in an indirect manner, so that it cannot be revealed accidentally. Personal information and all records of interested families not enrolled in the study will be destroyed by the trial coordinator by the end of participant recruitment.

Data with long-term value are stored in locked cabinets and secure servers of the University of Helsinki and (in the case of the biological samples) Folkhälsan Research Centre for 10 years from the onset of the project, and after that for 15 more years without direct identifiers. The principal investigator is responsible for data publication, data protection, and information security. Only the members of the research team have access to the final trial dataset, and all research team personnel are trained in methodology and laboratory protocols.

### Risk assessment and monitoring

2.8

Participation in the interventions is expected to have no adverse effects on the health, wellbeing, or safety of the participating families. Therefore, a data monitoring committee has not been appointed. Nevertheless, intervention instructors are asked to report all negative occurrences in their intervention groups after each session, including, for example, minor accidents, crying or negative emotions, and conflicts between the participants (see Supplementary material). Additionally, all negative feedback or concerns raised by the parents that the intervention instructors, researchers, outcome assessors, or trial coordinator receive during the trial will be collected and stored by the trial coordinator.

Challenges in participant recruitment or attrition are expected to be minor, particularly regarding the primary outcomes (evaluated directly before and after the intervention) for three main reasons. Firstly, participation in the trial is expected to be engaging and rewarding, as pointed out in section 2.1.3. Secondly, several actions are taken to support adherence and commitment to the study, as described in section 2.4. Thirdly, the follow-up period of 1.5 years in total is considered relatively short. Challenges related to data loss are further minimized by using complementary outcome measures. For example, while EEG recordings may not always be successful in infancy and early childhood due to movement artifacts and participant refusal, parental questionnaires will still provide valuable information. Nevertheless, participant drop-outs and no-shows are carefully monitored (see also Supplementary material).

The following measures have been taken to ensure intervention fidelity and arm equivalence. The interventions have been planned in advance, and their execution is based on detailed lesson plans. Teachers are asked to report any deviations from the lesson plan or duration after each lesson. The teachers have planned the lessons together and meet regularly (1 h/month) during the interventions to harmonize their practices as much as possible. The authors PV and BA conduct lesson observations for all teachers. For more information, see Supplementary material.

### Data analysis

2.9

All analyses will preferably be conducted with intention-to-treat analysis, including all participants regardless of attendance rate and whether they completed the intervention. However, when deemed necessary, for example, due to the amount of missing data, the intention-to-treat analyses can be complemented by per-protocol analyses, i.e., with only those participants included who successfully completed the intervention (see 2.4).

In the primary analyses, the efficacy of the trial will be evaluated by investigating changes in the primary outcome measures between baseline and post-intervention assessments, based on an interaction between time (baseline vs. post-intervention) and intervention arm (music vs. circus).^2^ Main analysis methods will be linear mixed models and repeated-measures ANOVAs, with statistical significance defined as *p* < 0.05 and appropriate adjustments correcting for multiple comparisons. Linear mixed models are well-suited for accommodating missing data that may occur between assessment points through the use of maximum likelihood estimation, which allows all available data to contribute to the estimation of model parameters under the assumption of missing at random.

Additional secondary and exploratory analyses will be conducted. The possible moderating effects of intervention timing on the primary outcomes will be investigated by adding participant age and developmental status at intervention start as covariates or fixed factors to the primary analyses.^3^ The risk of dyslexia will be included in the statistical models as a fixed factor to account for its moderating effects on the primary outcomes, and additional stratification will be made based on both the severity of parental dyslexia and genetic background (SNPs associated with dyslexia and language development will be entered as fixed factors, with children categorized into risk and non-risk subgroups according to their allelic variation). The possible mediating role of social–emotional factors on the primary outcomes will be analyzed. To further explore factors moderating intervention efficacy, the effects of intervention timing (morning or evening), adherence to the intervention (attendance rate), motivation towards the intervention (see Supplementary material), as well as the social structure and atmosphere of the intervention (see Supplementary material) will be additionally considered in the analyses of primary outcomes. Similarly, the role of home activities, especially those related to music and literacy, as well as hobbies that the child participates in, will be taken into account in the primary analyses. Further analyses will be conducted to investigate potential effects of the intervention on intervention-specific outcomes, including neural music processing and musical abilities (music intervention) and motor abilities (circus intervention).

For all statistical analysis models, we will examine the necessary assumptions using appropriate diagnostic tests. Furthermore, if non-linear patterns of change in the outcomes are indicated across the three assessment points, we will consider the use of, for example, structural equation modeling approaches to more flexibly capture individual differences in change trajectories.

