#### Sample size

2.1.3

The target maximum sample size is *N* = 200 infants. To reach a balanced sample, the aim is to recruit 30–50 participants for each stratum (see 2.2). A power analysis indicated that 50 participants per intervention arm are needed to evaluate the primary outcome measures, given a repeated measures ANOVA with a two-within (time of assessment: baseline vs. post-intervention) x two-between (intervention arms) design, a small effect size, Hedge’s g of 0.31 [based on the meta-analysis (Neves et al., 2022)], an alpha level of 0.05, a power of 0.8, and an expected correlation of 0.7 between the repeated measures.

Based on our previous longitudinal intervention study [see Virtala et al. (2022), Virtala and Partanen (2018), and Virtala et al. (2023), where 76% of the original sample recruited at birth participated in EEG and behavioral tests at 28 months], and given the engaging and rewarding nature of both intervention arms and the lack of a passive control group, we expect a low drop-out rate of a maximum of 20% for the primary outcome measures, including baseline and post-intervention assessments. This percentage includes families who will refuse participation before completing post-intervention assessments or who will not successfully complete some of the baseline or post-intervention assessments. Therefore, we assume that a sample size of *N* = 120 will be sufficient for reliably evaluating the primary outcomes of the interventions in the repeated measures ANOVA framework. However, it is relevant to note that this sample size is not optimal for probing the interaction of intervention arm x time in the linear mixed models or for the additional analyses (including, e.g., subgrouping based on participant characteristics or mediation analyses, see 2.9). To additionally calculate sufficient sample sizes per intervention arm for the planned linear mixed models, specifically considering the studied interaction of intervention arm x time, simulations were run according to Caldwell et al. (2022) and Kumle et al. (2021). These simulations suggested a larger required sample size of 100 per arm in order to ensure a power of 0.8, considering the values described above. We therefore aim for a sample size between 120 and 200, as large as practically possible within the 1.5-year time frame for participant recruitment.

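### The primary time-by-arm test compares raw change scores; adjusting for baseline would be at least as precise, with a 15% gain at the protocol's r = 0.7 if the SDs at both visits are equal

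*Protocol article*

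**What the plan says.** Section 2.9 (Data analysis) fixes the primary contrast: change in the primary outcomes from baseline to post-intervention, "based on an interaction between time (baseline vs. post-intervention) and intervention arm (music vs. circus"). On the model it says: "Main analysis methods will be linear mixed models and repeated-measures ANOVAs".

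Section 2.1.3 (Sample size) powers the same contrast, a "two-within (time of assessment: baseline vs. post-intervention) x two-between (intervention arms) design", with "a small effect size, Hedge’s g of 0.31", "an alpha level of 0.05, a power of 0.8" and "an expected correlation of 0.7 between the repeated measures". Simulations for the arm-by-time term in the mixed model gave 100 per arm.

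The covariates listed in section 2.9 include age, developmental status, dyslexia risk, session timing, adherence and home activities. The text shown neither adjusts the post-intervention score for its own baseline value nor holds the baseline mean equal across arms. The footnote attached to the quoted sentence is not shown.

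Section 2.6 (Trial timeline) reports that recruitment has closed. Of 184 infants randomised, 154 attended baseline (75 music, 79 circus).

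**The concern.** A change score subtracts the whole baseline value, which gives the baseline a coefficient of exactly 1. The best coefficient is the regression slope of post on baseline, and unless that slope happens to be 1, subtracting the full baseline adds noise. In a randomised comparison the baseline-adjusted analysis targets the same effect with equal or smaller variance.

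This matters here because the protocol's own simulations ask for 100 infants per arm for this test, 154 in total have a baseline, and no more can be recruited. Section 3.1 (Limitations) also expects the spread of ages to make small effects harder to detect. Better use of baseline scores already collected is one of the few ways left to recover power.

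**Working it through.** **Inputs.** From section 2.1.3: effect d = 0.31, r = 0.7, alpha 0.05, power 0.80. From section 2.6: 75 and 79 infants with a baseline. Assumptions: two-sided test; d expressed in units of the single-visit SD; equal SDs at the two visits for steps 1 to 3.

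**1. Reproduce the plan's figure.** With complete data, the interaction is a two-sample test on change.
- Variance of change = 2(1 − r) = 2 × 0.3 = 0.60, so SD = 0.775.
- n per arm = 2 × 0.60 × (1.960 + 0.842)² / 0.31² ≈ 98.0, rounded up to 99. The noncentral t also gives 99.

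This matches the stated 100 per arm and confirms that the mixed-model interaction was powered as a change-score test. The other figure in section 2.1.3, 50 per arm, does not reproduce for this contrast (power 0.52 at 50 per arm); that is a separate matter.

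**2. Adjust for baseline.**
- Residual variance = 1 − r² = 1 − 0.49 = 0.51, so SD = 0.714.
- Variance ratio = 0.51 / 0.60 = 0.85, a loss of 15% with the change score.
- n per arm = 84 (normal approximation) or 85 (noncentral t).

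**3. Power (noncentral t).**

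| Infants analysed | Change score | Baseline-adjusted |
|---|---|---|
| 100 / 100 | 80% | 86% |
| 75 / 79 | 69% | 76% |
| 60 / 63 (20% loss) | 60% | 67% |

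A simulation of 20,000 trials with 100 per arm gave power of 0.805 against 0.864 and a variance ratio of 0.853. Both estimators averaged 0.31.

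**4. Vary the correlation (equal SDs).** The loss is 1 − (1 + r)/2: 25% at r = 0.5, 20% at 0.6, 15% at 0.7 and 10% at 0.8.

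**5. Vary the SD ratio (r = 0.7).** Let k be the post SD divided by the baseline SD, with the baseline SD set to 1. The variance of change is 1 + k² − 1.4k, and the adjusted variance is 0.51k². The loss is 1 − 0.51k²/(1 + k² − 1.4k), which equals (1 − 0.7k)²/(1 + k² − 1.4k). It cannot be negative, and it is zero only at k = 1/0.7 = 1.43.

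| k | Loss |
|---|---|
| 0.8 | 37% |
| 1.0 | 15% |
| 1.2 | 3% |
| 1.43 | 0% |
| 2 | 7% |
| 3 | 21% |

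**The case against.** The strongest reply is that nothing here is an error. The interaction test is valid under randomisation, matches the hypothesis of larger improvement in the music arm, and agrees with the mixed-model sample size. That stands: the point concerns precision only, and a reader who inferred a biased or invalid primary test would go further than the documents allow.

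The size is also open. The protocol gives no SDs. Vocabulary may well spread out over six months, and at a ratio near 1.43 the loss vanishes. A flat 15% for every primary outcome is therefore not supported.

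Two stronger readings of section 2.9 are tempting. One is that repeated-measures ANOVA contradicts an aim of using all available data; but that wording describes a property of mixed models, not a rule for the whole trial. The other is that naming two methods yields two primary p-values per outcome; but the text does not say that both are run on every outcome.

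A further objection concerns the remedy. Plain ANCOVA needs both visits, so it drops infants with a failed EEG just as repeated-measures ANOVA does. Any baseline-adjusted analysis also relies on equal expected baselines. Here the allocation sequence was not concealed from the coordinator who assigned infants (section 2.2), allocation preceded baseline (section 2.1.1), and 30 of 184 randomised (16%) did not attend it. If true baselines differ, the two analyses estimate different quantities. Both cautions stand and shape the recommendation.

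**Conclusion.** The concern holds as a matter of efficiency. The planned interaction is a raw change-score comparison that, in large samples, at best ties with a baseline-adjusted one. At r = 0.7 with equal SDs it costs 15% of the information, or about 7 percentage points of power at the numbers available. Across SD ratios from 0.8 to 3 the loss ranges from 0% to 37%. The power figures rest on d = 0.31 in single-visit SD units, two-sided alpha 0.05 and equal SDs.

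The equivalence to a change score assumes a free baseline mean in each arm. A mixed model with a common baseline mean would already recover the loss, but the text shown does not specify one. The change is worth making; the trial's validity does not depend on it.

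**What to change.** Make the primary analysis, for each primary outcome, a linear mixed model of the two visits with a baseline mean common to both arms and separate variances at baseline and post-intervention. With complete data it is equivalent to ANCOVA on the post score, and it keeps infants with one missing visit. Report the adjusted mean difference at post-intervention with its 95% CI.

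Keep the unconstrained time-by-arm mixed model as a sensitivity analysis, because unconcealed allocation and attrition before baseline leave equal expected baselines less secure than usual. Repeated-measures ANOVA need not remain a main method: with complete data it gives the same interaction test, and otherwise it drops infants with a missing visit.

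No new data are needed. The cost is a dated, justified amendment to the analysis plan and registry entry, made before outcome data are examined by arm; section 2.6 has post-intervention assessments running from March 2025 to about March 2026. The price of the added precision is reliance on equal expected baselines.

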#### Primary outcomes

1.3.1

*H1:* Music intervention benefits language development.

It is expected that the music intervention group will show larger improvements in language abilities and neural speech processing between the baseline and post-intervention time points compared to the control intervention group. Language development will be evaluated with standardized parental questionnaires (validated parental report instruments), where a greater increase in the questionnaire scores is expected between the baseline and post-intervention assessments in the experimental (music) compared to the control arm (circus). Speech processing will be evaluated with ERPs and MMRs to speech sounds and their changes. ERPs and MMRs are hypothesized to display a more mature pattern in the experimental (music) than the control arm (circus) after but not prior to the intervention.

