Furthermore, in an optimal scenario, a standardized behavioral battery of musical abilities would be included at all three assessment points to show reliable intervention-specific effects on the behavioral level in addition to the neural level. Similarly, in the best case, a general cognitive/developmental status evaluation would be conducted at all assessment points to evaluate the possible discrepancies between it and language development. However, due to time constraints caused by the young age of the participants and in order to not burden the families with an excessive amount of laboratory visits, the behavioral assessment was restricted to language (and motor) development for which standardized behavioral tests exist for this age group. To complement this information, any concerns or diagnoses related to the child’s development are inquired from parents at all assessment points.

The inclusion of multiple outcome variables in the present trial can be considered both a strength and a limitation. The inclusion of several primary variables increases the risk of underpowered analyses and overly positive conclusions on intervention efficacy. It is also important to note the limitations of the sample size in reliably probing all the secondary and exploratory outcomes. Nevertheless, the strength of the approach is that the behavioral and neural measures can provide complementary information on early language development and a broader view of the specific benefits of the intervention. The clearly larger sample size compared to previous similar studies (Benasich et al., 2014; Gerry et al., 2012; Musacchia et al., 2017; Zhao and Kuhl, 2016; Zhao et al., 2022) enables preliminary exploration of many aspects that have been overlooked in earlier studies, including, for example, the role of participant age on intervention efficacy. These findings can provide important starting points for future, more focused studies.

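### The stated power of 0.8 is for one test at 0.05, but the primary set has up to 22 scores with no lead score and is to be corrected for multiplicity; the neural measures also have no stated sign

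*Protocol article*

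**What the plan says.** **Primary set.** Section 2.5.1 makes language development at baseline and post-intervention primary, measured by two parental questionnaires and by auditory ERPs and MMRs. Section 2.5.1.1 gives the CSBS ITC three subscales and a total. Of the FinCDI-LF it says: "It gives scores separately for expressive and receptive vocabulary size and for the gestures scale for non-verbal communication". Section 2.5.1.2 lists the obligatory responses P1 and N2 and the MMRs from a paradigm with three deviant types, and adds: "Peak latencies, mean amplitudes, and hemispheric lateralization of these responses are quantified from a fronto-central region of interest". No score is named as the lead.

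**Analysis.** Section 2.9 tests the time by arm interaction at p < 0.05, with "appropriate adjustments correcting for multiple comparisons".

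**Sample size.** Section 2.1.3 arrives at 50 per arm for a 2 x 2 repeated-measures ANOVA with Hedges' g of 0.31, "an alpha level of 0.05, a power of 0.8, and an expected correlation of 0.7 between the repeated measures". It then reports simulations for the linear mixed models that needed 100 per arm for a power of 0.8, based on the same values.

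**Direction.** Section 1.3.1 expects a larger rise in questionnaire scores with music. For the neural outcomes it says: "ERPs and MMRs are hypothesized to display a more mature pattern in the experimental (music) than the control arm".

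**Limitation conceded.** Section 3.1 states: "The inclusion of several primary variables increases the risk of underpowered analyses and overly positive conclusions on intervention efficacy".

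**The concern.** A power figure belongs to the significance level at which the test is carried out. The article promises a correction over several primary scores, but its sample size allows for one uncorrected test. A reader who takes the 0.8 at face value would expect each primary score to have an 80% chance of showing a true effect of g 0.31. After any correction the chance is lower, and how much lower depends on a family that the article does not delimit.

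The second half concerns H1 for the neural outcomes. A more mature pattern is not a sign. Up to 15 measures of amplitude, latency and lateralization can each move either way, and the article does not say which way counts as benefit for which measure. A significant result would then need to be interpreted after the fact before it could be called support for H1.

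**Working it through.** **1. Count of listed primary scores (sections 2.5.1.1 and 2.5.1.2).**
- CSBS ITC: 3 subscales + 1 total = 4.
- FinCDI-LF: expressive, receptive, gestures = 3.
- ERPs/MMRs: P1, N2 and 3 MMRs = 5 responses; latency, amplitude and lateralization for each gives up to 5 x 3 = 15.
- Questionnaires: 4 + 3 = 7. All: 7 + 15 = 22 at most.

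**2. Inputs for power.** From section 2.1.3: g = 0.31, correlation 0.7, alpha 0.05, power 0.8, maximum dropout 20%. From section 2.6: 75 (music) and 79 (circus) at baseline. Assumed: a two-sided test, since sidedness is not stated.

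**3. Model.** With two time points, the arm by time interaction is a two-sample comparison of change scores.
- SD of change = sqrt(2 x (1 - 0.7)) = sqrt(0.6) = 0.775.
- Standardized difference in change = 0.31 / 0.775 = 0.400.

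**4. The plan's own figures.**
- n per arm = 2 x (1.960 + 0.842)^2 / 0.400^2 = about 98; rounded up, and confirmed with the noncentral t distribution, 99.
- This matches the simulated 100 per arm, where power is 80%. The match is at one two-sided test at 0.05, so that figure contains no multiplicity allowance.
- The 50 per arm is not reproduced by this model, which gives 51% power with 50 per arm. That is a separate matter; its stated alpha is also 0.05.

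**5. Power for one given score at corrected levels.** Noncentral t with noncentrality 0.400 x sqrt(n1 x n2 / (n1 + n2)): 2.83 for 100/100, 2.48 for 75/79 and 2.22 for 60/63. The last pair is 0.8 x 75 = 60 and 0.8 x 79 = 63.2.

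| Alpha for the test | 100 per arm | 75/79, no dropout | 60/63, after 20% dropout |
|---|---|---|---|
| 0.05 (as in 2.1.3) | 80% | 69% | 60% |
| 0.025 (two primaries) | 72% | 59% | 48% |
| 0.05/7 = 0.00714 | 55% | 41% | 31% |
| 0.05/22 = 0.00227 | 40% | 27% | 19% |

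For 80% power the model needs 120 per arm at 0.025, 158 at 0.05/7 and 192 at 0.05/22.

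**6. Chance that at least one score passes.** This differs from step 5. Suppose all 22 scores carry g 0.31, Bonferroni over 22 is used, and the scores are equally correlated (an assumption; the article gives no correlation between scores). By simulation with 75/79, at least one score passes in about 93% of trials at a correlation of 0.3 and about 71% at 0.7.

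**7. Direction.** Section 1.3 sets a superiority framework in favour of music, and section 1.3.1 gives all 7 questionnaire scores a direction. The same section gives the neural measures only the maturity wording, and section 1.3.2 couples more mature with enhanced. Section 1.1 reports enhanced positive MMRs as the benefit in the team's earlier study of younger infants. None of these passages assigns a sign to each amplitude, latency or lateralization measure in this trial.

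**The case against.** **The count and the family are not the plan's.** The article lists what the instruments yield, not 22 tests. In a mixed model or ANOVA, deviant type or hemisphere could be a within-subject factor. Nothing says that the correction is Bonferroni or spans 22 scores. This stands: 7 and 22 are assumed families, and 22 is a worst case. But even two primaries at 0.025 give 72% with 100 per arm, so the mismatch does not depend on the larger count.

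**The details may be elsewhere.** The correction method and family could be in a statistical analysis plan that is not shown, and a footnote to the primary-analysis sentence is not reproduced. This also stands, and their absence is not the point made here. No later choice of method changes the fact that the published power was computed at 0.05.

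**False positives.** A reader might infer that the trial runs a high risk of a chance finding: 22 independent tests at 0.05 would give 1 - 0.95^22 = 68%. The article does not support that reading. It commits to correction, and the scores are correlated; the CSBS ITC total sits beside its own subscales.

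**Hopeless power.** A reader might infer from the 27% that the trial can confirm almost nothing. That confuses power for one given score with the chance that at least one passes, which is far higher (step 6).

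**Direction.** A reader might infer that no direction is given at all, or that the authors would accept either direction for the ERPs. Neither is stated. The questionnaires have a direction, and the earlier MMR result hints at one for amplitude. The gap is limited to the missing sign per neural measure.

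**Disclosure.** The authors concede the risk in section 3.1. The promised correction meets the false-positive half of it; nothing in the article adjusts the sample size for the power half.

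**Conclusion.** The point holds in this form. The primary set has no lead score, section 2.9 promises a multiplicity correction, and both sample-size figures in section 2.1.3 rest on one test at an unadjusted 0.05. The stated 0.8 therefore does not describe the corrected analysis. Even with only two primaries, power per score is 72% at 100 per arm, and 59% falling to about 48% in the sample actually reached. The lower figures for 7 or 22 scores are bounds under assumed Bonferroni families.

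The results rest on the protocol's g and correlation, a two-sided change-score test, and equal effects across scores where the chance of any success is quoted. Separately, the neural part of H1 has a claimed benefit but no sign per measure. The issue should be settled before unblinding; it does not invalidate the trial.

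**What to change.** Before arm codes are opened, and with the change recorded at the registry as section 2.1.1 provides for protocol modifications:

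1. Designate a small confirmatory set, for example one questionnaire score and one ERP measure (one response, one parameter), with the expected sign of each. Which scores to choose is for the team.
2. State the family-wise procedure for that set (Holm would do) and say that H1 is judged on it.
3. Treat the remaining scores as secondary.
4. Restate power at the corrected alpha for the analysable sample. With two primaries at 0.025 that is about 48% per score at 60/63, or 59% if nobody is lost.

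Recruitment has closed, so none of this involves enrolling more infants or collecting new data. The cost is that fewer scores can carry the confirmatory claim and that the quoted power is lower than 0.8.
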